## Abstract

**Background:**

Multiple randomized controlled trials (RCTs) show that behavioral lifestyle interventions are effective in improving diabetes management and that comprehensive risk factor management improves cardiovascular disease (CVD) outcomes. The role of technology has been gaining strong support as evidence builds of its potential to improve diabetes management; however, evaluation of its impact in minority populations is limited. This study intends to provide early evidence of a theory-driven intervention, Tablet-Aided BehavioraL intervention EffecT on Self-management skills (TABLETS), using real-time videoconferencing for education and skills training. We examine the potential for TABLETS to improve health risk behaviors and reduce CVD risk outcomes among a low-income African American (AA) population with poorly controlled type 2 diabetes.

**Methods:**

The study is a two-arm, pilot controlled trial that randomizes 30 participants to the TABLETS intervention and 30 participants to a usual care group. Blinded outcome assessments will be completed at baseline, 2.5 months (immediate post-intervention), and 6.5 months (follow-up). The TABLETS intervention consists of culturally tailored telephone-delivered diabetes education and skills training delivered via videoconferencing on tablet devices, with two booster sessions delivered via tablet-based videoconferencing at 3 months and 5 months to stimulate ongoing use of the tablet device with access to intervention materials via videoconferencing slides and a manual of supplementary materials. The primary outcomes are physical activity, diet, medication adherence, and self-monitoring behavior, whereas the secondary outcomes are HbA1c, low-density lipoprotein cholesterol (LDL-C), BP, CVD risk, and quality of life.

**Discussion:**

This study provides a unique opportunity to assess the feasibility and efficacy of a theory-driven, tablet-aided behavioral intervention that utilizes real-time videoconferencing technology for education and skills training on self-management behaviors and quality of life among a high-risk, low-income AA population with an uncontrolled dyad or triad of CVD risk factors (diabetes with or without hypertension or hyperlipidemia). The intervention leverages the use of novel technology for education and skill-building to foster improved diabetes self-management. The findings of this study will inform the process of disseminating the intervention to a broader and larger sample of people and can potentially be refined to align with clinical workflows that target a subsample of patients with poor diabetes self-management.

**Trial registration:**

The trial was registered in April 2014 with the United States National Institutes of Health Clinical Trials Registry (ClinicalTrials.gov identifier NCT02128854), available online at: http://clinicaltrials.gov/ct2/show/NCT02128854.

## Background

The southeastern “Diabetes and Stroke Belt” of the US has a high rate of mortality attributed to independent risk factors for cardiovascular disease (CVD) [1, 2], such as diabetes, hypertension, dyslipidemia, and stroke. South Carolina (SC) has one of the highest proportions of African American (AA) residents (28 %) compared to the national prevalence (13 %). In addition, AAs face higher risks of heart disease and stroke-related deaths more often than Whites. AAs are 67 % more likely to have diabetes and had a stroke mortality rate that was 56 % higher than the national average in 2006 [3]. Behavioral risk factors such as poor diet, physical inactivity, and low medication adherence are strongly linked to adverse CVD events. Racial/ethnic differences in CVD risk factors show AAs to have up to a twofold risk of poor control of glycemia, blood pressure, and lipids compared to Whites [4, 5]. Thus, minority populations, AAs in particular, are more likely to suffer poor diabetes and CVD outcomes [6–10]. Updated guidelines for secondary prevention of CVD present compelling evidence that comprehensive risk factor management (pharmacologic and behavioral interventions) improves survival, reduces recurrent events and the need for interventional procedures, and improves quality of life [11]. However, providers face increasingly limited time to focus on individual self-care among those with multiple comorbidities. This study’s approach focuses on enabling self-management behaviors through a multi-component, tablet-aided behavioral intervention that supports self-reliance and behavior change as a potential solution to lowering CVD risk among people with diabetes.

Multiple randomized controlled trials (RCTs) show that behavioral lifestyle interventions are effective in improving diabetes and CVD outcomes [12–16]. A review of three large clinical trials with multifactorial interventions targeting CVD risk among people with diabetes revealed significant improvements in achieving good diabetes self-management behaviors (control of blood pressure [BP], lipids, glycemia [glycosylated hemoglobin A1c, HbA1c], weight, and medication adherence) [17], suggesting that interventions targeting multiple CVD risk factors have a larger impact on CVD risk reduction than single risk factor interventions. Although multiple concurrent and consecutive behavior adjustments can be tremendously difficult to learn and to maintain for patients [18], cross-cutting approaches to multi-morbid conditions will help advance chronic disease management [19]. A systematic review of coping skills training and problem-solving interventions in people with diabetes showed significantly improved diabetes self-management for better metabolic outcomes [20, 21]. Ultimately, problem-solving skills become an integral part of self-management education that helps empower patients to identify problems, adopt strategies to take action, and modify their actions based on different circumstances [22]. The current literature supports the idea that patient-level factors are the key to disease management [23–25] and implementing behavioral interventions with problem-solving and skills training components in high-risk adults is effective in reducing CVD outcomes.

The role of technology has been gaining strong support as evidence builds of its effectiveness for diabetes management [26, 27]. The utility of advanced communication technology in health care is in facilitating medical encounters, increasing access to health care services, and broadening availability of resources, even among underserved populations. Several studies have shown at least equivalent effectiveness of computer-aided [28], telehealth [29, 30], and mobile-enabled interventions on improving diabetes self-care [31] and glycemic control [25, 27]. Another randomized study of 636 patients examined the extent of BP control attained through implementing a multi-component, telephone-delivered, behavioral self-management intervention, home BP monitoring, combined intervention, and usual care [32]. This study showed a significant BP-lowering effect from the combined intervention compared to usual care with a mean of 10 telephone calls (standard deviation, or SD = 3) and a mean call length of 16 minutes (SD = 7); the separate interventions showed no difference. Patients often prefer to rely on these information and communication modalities for access to health care resources and for initiating positive changes in their health behaviors. Yet, the role of technology in minority populations is limited to telehealth interventions that target problem-solving skills [33, 34], which reduces office visits but does not allow consistent daily support to facilitate learning adaptive behaviors for good diabetes self-management (DSM). Studies that focus on AA participants will help to fill a gap in the literature on how behavioral interventions can use technology to better impact self-management of diabetes and other cardiovascular risk factors in this specific subpopulation [25], which generally has poorer glycemic control and higher mortality rates [10]. The proposed study provides early evidence of the theory-driven, Tablet-Aided BehavioraL intervention EffecT on Self-management skills (TABLETS), using real-time videoconferencing for education and skills training, on improving chronic disease self-management (CDSM) behaviors and CVD risk among a high-risk, low-income AA population.

### Rationale

Resources are limited for many AAs in SC, given the disproportionately greater poverty and lower education among AAs compared to Whites [35]. Our pilot RCT will maximize the reach and effect of the intervention and will improve CDSM behaviors (physical activity, diet, medication adherence, self-monitoring) without exceeding available resources [18]. The TABLETS intervention targets control of these modifiable risk behaviors. We use motivational enhancement strategies for low-income AA adults to help them develop a skill set that achieves and maintains good behavioral and clinical outcomes. Potentially successful patient-focused strategies can utilize technology as a tool [31] for personalized learning experiences, and as rapidly interactive and mutually convenient modes of communication between patients and providers [36]. The proposed project will present early evidence of the effectiveness of a multi-component intervention targeting CDSM behaviors using a tablet-based delivery approach for high-risk, low-income AAs. Tablet-aided delivery of the behavioral intervention is best for several reasons: (1) the tablet has a larger visual display to facilitate use among older minority adults — the demographic at highest risk for diabetes, (2) there is greater accessibility of health services and resources for low income populations, and (3) technology-enabled intervention has the added value of convenience, portability, multi-tasking, and personalization, as studies show promising results with small improvements in clinical outcomes among people with diabetes [37, 38]. This project will yield valuable data in preparation for a large-scale RCT to assess whether the lifestyle intervention, in conjunction with tablets as a behavior augmentation tool, has strong potential for promoting long-term behavior change and chronic disease management in underserved populations.

### Study aim and objectives

The primary aim is to examine the efficacy of a multi-component TABLETS intervention on improving behavioral outcomes (physical activity, diet, medication adherence, self-monitoring) in high-risk, low-income AAs with type 2 diabetes using a pilot RCT design. The secondary aims examines the efficacy of the multi-component TABLETS intervention on improving CVD risk profiles and health-related quality of life among high-risk, low-income AAs with type 2 diabetes.

## Methods

The study is a two-arm, pilot RCT with 1:1 randomization of 60 AA participants. Blinded assessments are made at baseline (immediate post-randomization), 2.5 months, and 6.5 months (follow-up). Two booster sessions are delivered via tablet-based videoconferencing at 3 months and 5 months to stimulate ongoing use of the tablet device with access to intervention materials via videoconferencing slides and the web-based portal.

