The second method consists of referrals from physicians, other clinic staff such as nurses, or patients themselves in response to recruitment flyers for the study. The PI shares the goals of the study and inclusion/exclusion criteria with physicians and clinic staff during clinic administrative meetings. Physicians and clinic staff are asked to refer appropriate patients to the study research assistants. In addition, IRB-approved recruitment flyers are posted in prominent locations in the study clinics.

Regardless of the recruitment pathway, research staff members obtain written informed consent, complete screening for eligibility, and ensure that participants meet criteria for inclusion and participation in the study. The procedure and risks are explained to the patients and the consent form signed as per standard practice. Eligibility has been determined as meeting the following inclusion criteria: self-identified black or African American; age ≥45 years; clinical diagnosis of T2DM (by ICD-9 code of 250.xx) with an HbA1c ≥8 % at screening; clinical diagnosis of hypertension and blood pressure (BP) >140/80 mmHg at the screening visit or clinical diagnosis of hyperlipidemia and low-density lipoprotein cholesterol (LDL-C) >100 mg/dL at screening; able to communicate in English; residence in a 4G cellular service area; and access to a telephone (landline or cell phone). Exclusion criteria include mental confusion or impairment during screening using the validated Mini-Cog instrument [39]; participation in other clinical trials related to the subject area; alcohol or drug abuse/dependence; active psychosis; acute decompensation of chronic conditions that preclude participation; and life expectancy <6 months. Participants who meet eligibility criteria then complete the remainder of the assessment battery and undergo randomization.

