### Randomization

All participants are randomly assigned to one of the two study arms (n = 30 per arm) using a permuted block randomization method: (a) TABLETS intervention and (b) usual care (UC). Block size is varied to minimize the likelihood that the blind is broken. The randomization is stratified by baseline HbA1c levels (8–10 % versus >10 %). The RA collects eligibility information and enters the information into the study database via the secured study website. Once eligibility is confirmed, a computer program developed by the biostatistician ([name]) generates the intervention assignment based on the preprogrammed randomization scheme with the order of assignment placed in sealed envelopes until informed consent to participate is signed and eligibility criteria are met. All participants who are randomized are entered into the study database and analyzed according to CONSORT guidelines, as shown in Fig. 1 [40].

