### Study instruments and data collection schedule

See Fig. 3 for the study design and study flow and Tables 1, 2, and 3 for the data collection schedule, data collection measures, and data collection instruments, respectively. The RA, who was blinded to group assignment, conducted study assessments at baseline and at 2.5 and 6.5 months post-randomization. The NHE presented the randomized group assignment to each participant and performed the study intervention sessions. All blood samples were analyzed at the central laboratory of the academic medical center.

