**Fig. 3 Fig3:**
[figure not shown]
Study design and flow

**Table 1 Tab1:** Data collection schedule

Questionnaires/measurements	Screening visit	Baseline visit	2.5 months visit	6.5 months visit
Primary outcome measures				
Physical activity (GPAQ)		x	x	x
Diet (REAPS)		x	x	x
Medication adherence (MMAS)		x	x	x
Self-monitoring behavior		x	x	x
Secondary outcome measures				
HbA1c	x		x	x
LDL cholesterol	x		x	x
Blood pressure	x		x	x
CVD risk (FRS)		x	x	x
Quality of life (SF-12)		x	x	x
Process measures				
Knowledge/information		x	x	x
Motivation		x	x	x
Behavioral skills		x	x	x
Self-efficacy		x	x	x
Empowerment		x	x	x
Tablet usability		x	x	x
Covariates				
Patient demographics	x			
Medical comorbidity (chronic health conditions – BRFSS)		x	x	x
Social support (MOS)		x	x	x
Health literacy (s-TOFHLA)		x	x	x
Brief literacy screener (Chew)		x	x	x
Depression (PHQ-9)		x	x	x

**Table 2 Tab2:** Data Collection for Outcome Measures

Outcome	Test	Measurement
Primary outcome measures	Physical activity	Measured by the 16-item Global Physical Activity Questionnaire (GPAQ) [57]
	Diet	Dietary intake assessed using the Rapid Eating and Activity Assessment for Participants Short Version (REAP-S) [58]
	Medication adherence	Measured with the 8-item self-report Morisky Medication Adherence Scale (MMAS) [59]
	Self-monitoring behavior	Measured with the Summary of Diabetes Self-Care Activities (SDSCA) scale [60]
Secondary outcome measures	HbA1c, low-density lipoprotein cholesterol (LDL-C)	Blood specimens obtained at baseline, 2.5 and 6.5 months visits
	Blood pressure (BP) measurements	An average of three BP readings done in 2-minute intervals obtained at baseline, 2.5 and 6.5 months by a trained RA using automated BP monitors (OMRON IntelliSense^TM^ HEM-907XL) with the patient seated comfortably for 5 minutes prior to the measurements
	Cardiovascular disease risk	Framingham Risk Score (FRS) estimates the 10-year risk of “hard” coronary heart disease outcomes (myocardial infarction, death) [45]
	Quality of life	The SF-12 is a valid and reliable instrument to measure functional status and will be used to assess quality of life at baseline, 2, and 6 months assessments. The SF-12 items reproduce at least 90 % of the variance in PCS-36 and MCS-36 scores [49]

**Table 3 Tab3:** Data Collection for Intermediate Measures and Covariates

Measure	Data collected	Method
Process and behavioral measures	Information	Measured by the 29-item CVD Knowledge Questionnaire [61]

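### The article places the baseline assessment both after and before randomization, so self-reported baselines may be given by participants who already know their arm

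*Protocol article*

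**What the plan says.** Four sections of the protocol article bear on the order of events.

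- **Methods (opening paragraph):** "Blinded assessments are made at baseline (immediate post-randomization), 2.5 months, and 6.5 months (follow-up"). Baseline comes after randomization.
- **Trial population and recruitment:** "Participants who meet eligibility criteria then complete the remainder of the assessment battery and undergo randomization". Read naturally, baseline comes first.
- **Randomization:** the assignment is generated once eligibility is confirmed, "with the order of assignment placed in sealed envelopes until informed consent to participate is signed and eligibility criteria are met". A completed baseline is not named as a condition.
- **Study instruments and data collection schedule:** "The RA, who was blinded to group assignment, conducted study assessments at baseline and at 2.5 and 6.5 months post-randomization", and "The NHE presented the randomized group assignment to each participant and performed the study intervention sessions". The timing of disclosure relative to the baseline visit is not given.

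Table 1 schedules all four primary measures (GPAQ, REAP-S, MMAS and self-monitoring by SDSCA) and the SF-12 at the baseline visit, not at screening. It marks HbA1c, LDL-C and blood pressure at screening and not at the baseline visit. Table 2 describes HbA1c and LDL-C as "Blood specimens obtained at baseline, 2.5 and 6.5 months visits" and likewise places a blood pressure reading at baseline. Randomization is stratified by baseline HbA1c.

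**The concern.** The two orders cannot both hold, and both stand in the current Methods text. The difference matters because the primary outcomes come from instruments that the participant answers. The only person stated to be blinded is the research assistant. The participant learns the arm, and the arms differ visibly: a tablet, monitoring devices and coaching against usual care with no attention control.

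If the arm is known when the baseline questionnaires are completed, reported diet, activity, adherence or self-monitoring may shift through expectation, disappointment or a wish to please. The primary hypothesis is stated as greater improvement, and the planned GLMM compares trajectories between arms. Both use the baseline as the anchor. A baseline that depends on allocation would feed into the estimated change, and adding covariates later would not remove it. The sample size section says that small differences may be read as a signal justifying a larger trial, so a modest bias could create or hide such a signal.

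**Working it through.** **1. Textual check.** The article gives no figure to reproduce on this point, so the sections are set side by side.

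| Section | Order implied | Settles when the arm is known? |
|---|---|---|
| Methods, opening paragraph | randomize, then baseline | No: it speaks of randomization, not disclosure |
| Trial population and recruitment | battery, then randomize | Yes, if followed: the arm does not yet exist at baseline |
| Randomization | consent and eligibility, then release | No: baseline is not a condition |
| Study instruments | NHE discloses, research assistant assesses | No: timing of disclosure not given |

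Under the recruitment section the problem cannot arise. Under the Methods overview it can, unless the NHE waits until the baseline visit is over.

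**2. Which measures are exposed.** By Table 1, these are the self-report measures first taken at the baseline visit: GPAQ, REAP-S, MMAS, SDSCA and SF-12. HbA1c, LDL-C and blood pressure are taken at screening, before randomization. Stratifying on HbA1c also requires that value in advance.

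**3. Illustrative size.** The inputs are 30 per arm (from the article) and two assumptions that have no source in it: a baseline shift d of 0.1, 0.2 or 0.3 SD in one arm only, and a baseline to follow-up correlation r of 0.5. Outcomes are scaled to SD 1.

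*Change score.*
- SD of change = sqrt(2(1 − r)) = sqrt(2 × 0.5) = 1
- SE of the difference = sqrt(2/30) = 0.258
- Bias = d

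*ANCOVA.*
- Residual SD = sqrt(1 − r²) = sqrt(0.75) = 0.866
- SE = 0.258 × 0.866 = 0.224
- Bias = r × d = 0.5d

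| Shift d (SD) | Change: bias/SE | ANCOVA: bias/SE |
|---|---|---|
| 0.1 | 0.1/0.258 = 0.39 | 0.05/0.224 = 0.22 |
| 0.2 | 0.2/0.258 = 0.77 | 0.10/0.224 = 0.45 |
| 0.3 | 0.3/0.258 = 1.16 | 0.15/0.224 = 0.67 |

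**4. Where the bias does not reach.** The data analysis section also plans contrasts of least squares means at 2.5 and 6.5 months. If baseline enters the model as a repeated outcome with a separate mean for each arm and visit, a baseline shift in one arm is absorbed by that arm's baseline mean. With complete data, the contrast at follow-up does not move.

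**The case against.** The strongest reply is that the Methods wording is a slip: a parenthesis in a short design summary, whereas the recruitment section gives the operational sequence. Separate staff assess and disclose, and being randomized is not the same as being told. A condensed article need not repeat in the Randomization section a condition that it has already implied elsewhere.

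Much of this stands. A slip is plausible, and the omission in the Randomization section would not be a defect by itself. It matters only because that section could have settled the conflict and does not. Separate roles protect against assessor bias, not against a participant who knows the arm.

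Three stronger readings are tempting, and the documents do not support them.

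- *That baselines were taken after disclosure.* The Methods overview permits this but does not show it.
- *That usual-care participants who leave on learning their arm would have no baseline, which would undermine the intention-to-treat set.* HbA1c, LDL-C, blood pressure and demographics are collected at screening, so such participants would lack only the baseline-visit measures. The set is defined as all randomized participants, the GLMM is chosen partly because it accommodates missing data, and no differential exit is documented.
- *That every planned comparison would be biased.* Step 4 of the working shows one that would not be.

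It is also fair to say that recruitment was 92% complete at submission. With 0.92 × 60 ≈ 55 enrolled, a new rule would reach only about 5 participants, so the retrospective check carries more weight.

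**Conclusion.** The contradiction on the order of baseline and randomization is certain, and no other section resolves it. That it caused bias is not established: this depends on which order was used and on when the NHE disclosed the arm. If the Methods overview describes practice and disclosure came first, change-from-baseline and baseline-adjusted comparisons of the self-report outcomes are open to bias in a direction the article does not allow one to determine.

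At an assumed shift of 0.2 SD, the bias would be 0.77 SE for change scores and 0.45 SE for ANCOVA. The ranges in the working rest wholly on the assumed shift and correlation, and they show scale rather than an estimate.

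The difference between Tables 1 and 2 over HbA1c, LDL-C and blood pressure is a minor matter of labelling. Using a screening value as baseline is ordinary.

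**What to change.** 1. **Reconcile the text to practice.** Make the Methods overview, the recruitment section, the Randomization section and the data collection section state one order, namely the one actually used, and say when the NHE discloses the arm. Changing the Methods wording to put baseline before randomization without checking could misreport the trial.
2. **Remaining enrolment.** Require the baseline battery to be complete before the envelope is opened and the arm disclosed.
3. **Participants already enrolled.** Compare baseline dates with randomization and disclosure dates where these were recorded, and report how many had a baseline after disclosure. The article does not say that envelope-opening times are kept, so report any gap.
4. **If there are any such baselines,** add a sensitivity analysis that does not rely on them. Set them to missing in the GLMM or, if all are affected, compare follow-up means without baseline adjustment.
5. **Minor.** State that screening HbA1c, LDL-C and blood pressure serve as the baseline values, so that Tables 1 and 2 agree.

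The cost is protocol wording, a short instruction to staff, a date check in the study database and possibly one further analysis. No added visits or participants are needed.
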